### Participants’ timeline

Figure 2 provides an overview of the participants’ timeline. Patients in the intervention group receive the decision aid prior to the appointment at the outpatient clinic. Patient follow-up is finalised after the patient has completed the final questionnaire. Patients receive the final questionnaire 6 weeks after the treatment or, in case of conservative treatment, 6 weeks after the decision-making consultation.

**Fig. 2 Fig2:**
[figure not shown]
Participants’ timeline of actions during the trial. ┼: One week. *: Intervention group. ^: In case of conservative treatment. SF12: Short form health survey. CPS: Control preference or perception scale. DCS: Decisional conflict scale. SDM: Shared decision-making

### Sample size

Sample size calculations are based on a clinically relevant difference in the use of SDM during consultation before and after introduction of the DSTs. The systematic review of Couët et al. [31] found a mean increase from 23 (SD 14) to 34 (SD 8) of SDM scored with the 5-item OPTION instrument. An 11 out of 100 points increase of the 5-item OPTION instrument seems a meaningful improvement as it means an increase from a ‘minimal’ to a ‘moderate’ effort to involve patients in the decision-making process [31]. A larger increase would, of course, be even more clinically relevant and would require fewer patients, but this is less likely to reach. With a significance level of 0.05 and a power of 90%, a total sample size of 58 patients is required.

This number needs correction for the stepped-wedge design with cluster randomisation, as opposed to an individual patient randomisation. The total sample size from the power analysis is to be multiplied by the design effect for a stepped wedge trial. The pre-specified number of 5 steps (i.e. 6 time periods) and 5 clusters results in 58/(6*5) = 2 patients, per cluster per time period. Assuming an intermediate-level intra-cluster correlation of 0.01, the stepped wedge design effect is 1.944 [32]. Thus, the total sample size needed in this trial is 58 × 1.944 = 113 patients per disorder. Since four different vascular diseases are studied, there are actually four trials in one trial. Therefore, a multiplication of the total sample size by 4 is necessary, which leads to 452 patients. To adjust for a loss-to-follow-up of 10%, the study aims to include a total of 502 patients.

### Recruitment

All consecutive patients visiting the outpatient clinical of participating medical centres are screened for eligibility. Eligible patients are contacted by the researcher, nurse practitioner or surgeon and informed about the trial via the informed consent materials. The patient is given a minimum of 2 days to consider participation. Next, the patient is asked to participate in the study and to sign the informed consent form.

### Allocations

Participating medical centres are randomised into five different clusters, containing three centres. These clusters are again randomised every 2 months thereafter to decide which cluster is next to start applying the DSTs, as shown in Fig. 1. The researchers evaluate at each randomisation instance whether sufficient patients have been included in the trial. If inclusion rate falls behind, randomisation of the next cluster to use the DSTs is delayed for another 2 months. The researchers randomise the participating centres and clusters by drawing lots stating the name of a participating centre or cluster from an opaque container.

### Blinding

Due to the nature of this study it is not possible to blind patients or vascular surgeon, since they actively use the intervention. However, the cluster randomisation design does reduce potential contamination of information among the participating vascular surgeons. It is also not possible to blind the researchers scoring the five OPTION items on audio-recordings. The use of consultation cards and decision cards is audible and most vascular surgeons will inquire whether the patient has used the decision aid.

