### Interventions

The intervention comprises a set of DSTs, developed to help both vascular surgeons and patients to improve SDM. Use of the DSTs is compared to standard care at the level of individual participants. Standard care may include informative leaflets or websites that participating medical centres already provide to their patients.

The DSTs studied here are decision aids, consultation cards, decision cards and a practical training. The patient advocacy society (Heart and Vascular Group) and the Dutch professional society (Dutch Society for Vascular Surgery) provided intellectual support for the development of the DSTs. The Netherlands Organisation for Health Research and Development provided financial support (ZonMw, grant 516,022,506). The participating centres may decide which combination of DST they prefer to use.

*Decision aids* are validated web-based applications that provide patients with information about their disease and treatment options. In addition, it has an interactive section in which the patient is encouraged to consider what he or she believes is important when deciding on a treatment strategy [9, 17]. Patients receive the decision aid prior to the decision-making consultation via a personalised web link. The researchers automatically receive the answers given by patients in the decision aid regarding their disease-specific knowledge and treatment preferences. The following link provides access to the English version of the Dutch decision aid used in this study for patients with an AAA: https://sdmstaging.medify.eu/surgery1/index_da-aortic-aneurysm_en.html

More information about other available decision aids is provided at the website of the Ottawa Hospital Research Institute [18].

*Consultation cards* are validated tools, also known as Option Grids™ [19]. These are A4-sized paper sheets showing questions -with their answers- that patients most frequently ask about the treatment options, presented in a table format. Vascular surgeon and patient discuss the consultation cards during the consultation. The order in which the patient wants to discuss the questions provides insight into the aspects patients find relevant to them personally when deciding on a treatment strategy [11]. Table 3 shows the consultation card used in this study by vascular surgeons for patients with symptoms of intermittent claudication. More information about other available decision aids is provided at the website of the Dartmouth Institute [20].

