### Outcomes

The primary outcome is the level of SDM during the consultation as scored with the 5-item Observing patient involvement (OPTION) instrument [23]. The 5-item OPTION instrument allows researchers to objectively assess the level of patient involvement in the decision-making process as scored from audio-recordings of the consultations [24]. If the vascular surgeon and patient need more than one consultation to reach a treatment decision, all consultations are audio-recorded and scored as one consultation. Afterwards, two researchers independently score the five OPTION-items on a five-point scale. The cumulative OPTION-score is expressed on a 100-point scale.

Baseline characteristics, i.e. age, gender, diagnosis, highest level of education, employment status, social status, and ethnicity, are collected from the patients using a questionnaire before consultation.

Secondary outcomes are patients’ disease specific knowledge, decisional conflict, quality of life, and SDM as perceived by patients, SDM as perceived by vascular surgeons, the treatment decided upon, the implementation of DSTs, and process measures.

The patients’ disease-specific knowledge is scored directly after the consultation. The questions test whether patients correctly understood the information presented in the decision aid or received during the consultation.

Decisional conflict in patients is scored directly after the consultation and is repeated 4 weeks after consultation in which the treatment decision is made [17]. If an endovascular or open surgical treatment takes place within 4 weeks, decisional conflict is scored just before treatment. The decisional conflict in patients is scored using the 16-item Decisional Conflict Scale (DCS) [25].

Quality of life in patients is scored directly after consultation and again 6 weeks after treatment with the Short Form Health Survey (SF12) [26].

SDM as perceived by patients is scored directly after consultation using the SDM-Q-9 questionnaire, the 3-item CollaboRATE questionnaire, and the one-question Control Preference Scale and Control Perception Scale (CPS) [27–29]. The Control Preference Scale documents the desired amount of patient involvement and is scored before the consultation. The Control Perception Scale assesses the actually perceived amount of patient involvement and is scored after the consultation.

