SDM as perceived by vascular surgeons is scored after the consultation using the SDM-Q-DOC questionnaire and the Control Perception Scale [29, 30].

The treatment decided upon is derived from the audio recording of the consultation. The actually received treatment is obtained from the participating vascular surgeon or centre.

The extent in which DSTs are implemented is determined by scoring the number of times a specific tool is used as recorded by the audio recording (consultation card and decision cards). Successful use of the decision aid is defined as completion of the decision aid by the patient. Completion and time to complete is recorded automatically when patients access the decision aid via the provided link.

Process measures studied are the number and duration of consultations necessary to decide upon a treatment, as obtained from the audio recording(s) or from the participating vascular surgeon or centre.

All outcomes mentioned above are evaluated at the individual participant level.

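### The Blinding section rules out blinding of the OPTION scorers altogether, but its reasons exclude only full blinding to condition; coded files and a random scoring order remain possible and would protect the primary outcome cheaply.

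*Protocol article*

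**What the plan says.** The Outcomes section makes an observer rating the primary endpoint: "The primary outcome is the level of SDM during the consultation as scored with the 5-item Observing patient involvement (OPTION) instrument". The safeguard it names is double rating: "Afterwards, two researchers independently score the five OPTION-items on a five-point scale".

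The Blinding section then says of these raters: "It is also not possible to blind the researchers scoring the five OPTION items on audio-recordings". Its reason follows: "The use of consultation cards and decision cards is audible and most vascular surgeons will inquire whether the patient has used the decision aid". No partial masking is described there.

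Four other statements bear on the point:

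- Interventions: "The participating centres may decide which combination of DST they prefer to use". The tool mix therefore differs between centres.
- Outcomes: implementation is measured by "scoring the number of times a specific tool is used as recorded by the audio recording", so card use is itself an outcome that is expected to vary between recordings.
- Allocations: clusters start the tools one after another, at intervals of about 2 months, and "The researchers randomise the participating centres and clusters by drawing lots". Whether these researchers are also the scorers is not stated.
- Statistical methods: the OPTION comparison is an unequal-variance t-test, with ANCOVA for baseline differences between patients. No period or rater term is named.

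**The concern.** The conclusion in the Blinding section is wider than its premises. Both premises concern what a rater hears. Neither bears on what a rater is told by the file label, or on the order in which files are scored, and the trial team controls both of these whatever the audio reveals. The second premise is stated for the majority of surgeons, so by the protocol's own account some intervention recordings carry no decision-aid cue. Since centres choose their tools, cards need not appear in every intervention recording either.

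Two kinds of bias are at stake:

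- **Expectation.** A rater who knows the condition may score it more generously. Hiding labels helps only where the recording itself does not give the condition away.
- **Rater drift.** Standards can move over a long scoring period. In a stepped wedge, control precedes intervention in every cluster. If scoring follows calendar order, drift therefore lines up with condition, and the t-test reads it as part of the tool effect.

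A second independent rater reduces the error of one individual. It does not remove a shift that both raters share.

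**Working it through.** **Step 1. Does the stated reason support the stated conclusion?**

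| What could be hidden from the scorer | Is it excluded by the reasons in Blinding? |
|---|---|
| Condition, where a card is heard or the decision aid is mentioned | Yes |
| Condition, where there is no audible cue | No |
| Centre, date and period on the file label | No |
| Order of scoring | No |

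Only the first row is ruled out.

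**Step 2. How far would drift pass into the comparison?** The documents give no figure for scoring bias, so there is none to reproduce. The layout comes from Sample size: 5 clusters, 5 steps, 6 periods. Assume that one cluster crosses per step, that cells are of equal size, and that scoring is in calendar order.

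- Cluster i (i = 1 to 5) is in control for periods 1 to i and in intervention for periods i + 1 to 6. This gives 15 control and 15 intervention cells.
- The period numbers of the control cells sum to 1 + 3 + 6 + 10 + 15 = 35, so their mean is 35/15 = 2.33.
- All 30 cells sum to 5 × 21 = 105, so the intervention cells sum to 70 and their mean is 70/15 = 4.67.
- The gap is 2.33 of the 5 intervals between first and last period: (35/15)/5 = 7/15 = 0.467.

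A linear drift of D points from first to last period therefore biases the unadjusted difference by 7/15 × D.

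**Step 3. What would that do to the test?** Take the SDs of 14 and 8 from Sample size and 452 analysed patients split equally, 226 per group. Ignore clustering, assume no true effect, and test two-sided at 0.05.

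- SE = √((14² + 8²)/226) = √(260/226) = 1.07.
- The chance of a significant result under bias b is 1 − Φ(1.96 − b/SE) + Φ(−1.96 − b/SE).

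| Assumed drift D | Bias 7/15 × D | Share of 10 / 11 points | False significance |
|---|---|---|---|
| 1 | 0.47 | 5% / 4% | 7% |
| 2 | 0.93 | 9% / 8% | 14% |
| 3 | 1.40 | 14% / 13% | 26% |
| 5 | 2.33 | 23% / 21% | 59% |

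The two yardsticks are the 10 points of the Abstract and the 11 points of Sample size. With 29 per group (half of the 58 patients required before the design effect, for one disease), SE = √(260/29) = 2.99, and D = 5 gives 12%.

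**Step 4. What is a D of 5 on this scale?** If items are coded 0 to 4 (an assumption), one category on one item is 100/(5 × 4) = 5 points. D = 5 would then be an average movement of one category on one item over the whole scoring period. This is a unit conversion, not an estimate of how far raters drift.

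**The case against.** A reader might infer that nothing is masked, that scorers see centre and date, and that they work through the recordings in calendar order. The article says none of this. It states only that scoring takes place after the consultations. Data management adds that patient data are held under a code, with the key restricted to the principal investigator and authorised researchers. That does not show the scorers are masked, since they may be among those authorised, but it argues against the stronger reading. File labels and rater procedure are also details that an article may leave to the full protocol, so silence on them is not a fault. The point rests on the categorical sentence the article does contain.

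A reader might also infer that bias of this kind goes unchecked into the primary outcome and could never be removed. Double scoring limits part of it, and a period term, or rescoring of a random subset, could address calendar drift. The stated analysis names neither, but that is a separate matter of analysis.

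Three further objections stand:

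- A centre using only the decision aid would not usually yield silent recordings, because most surgeons are expected to ask about it. On the protocol's account, recordings without a cue are probably a minority.
- Removing labels cannot remove voices or spoken names, which may reveal the surgeon or centre.
- Where a tool is heard, masking leaves expectation bias in place. The protocol discloses this openly.

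None of these touches the order of scoring. A random order breaks the link between drift and condition even if every tool is audible.

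**Conclusion.** The point holds in a limited form. Full blinding to condition is not achievable, and the protocol is right to say so. Its wording goes further and excludes masking that its own reasons do not exclude, on a primary outcome that depends on rater judgement.

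The possible size under calendar-order scoring is 7/15 of whatever drift occurs, for example 0.9 points for D = 2 and 2.3 points for D = 5. This rests on assumed drift that is linear and shared by both raters, equal cells, and an analysis without a period term. The recruitment-delay rule in Allocations could make the periods unequal and change the factor. The documents support no particular value of D, so these figures show sensitivity and are not an estimate of bias in this trial. The sample-size figures of 58, 113, 452 and 502 do not depend on the point.

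It is a cheap improvement to a stated design choice, not an error that invalidates the plan.

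**What to change.** 1. Give the audio files random codes, without centre, date or period on the label.
2. Have the same two researchers score all recordings in random order, mixing control and intervention and mixing periods. Form batches only once recordings from both conditions are available. A single random order after the last recording separates drift from condition most completely.
3. Preferably use scorers who take no part in drawing the lots.
4. Reword the Blinding section to say that full blinding to condition is not possible because tools may be heard, but that scoring is partially masked as above, and that expectation bias may remain where a tool is audible.
5. Do not rely on a comparison restricted to recordings without an audible tool. That subset is selected after randomisation, and a smaller effect in it could reflect non-use of the tools rather than unbiased scoring. Drop it or label it exploratory.

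The cost is relabelling work and later availability of scores. No extra raters or patients are needed.

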### Data collection methods

Trial data are obtained via questionnaires, audio recordings, the decision aid content management system, and participating vascular surgeons. Patients fill out the questionnaires either at their medical centre, at home via email, or on paper accompanied by a stamped self-addressed envelope.

### Data management

All obtained trial data are considered as confidential information and will not be distributed to third parties. Patient data are stored anonymously under a code. Only the principal investigator or researchers authorised by the principal investigator have access to the key file.

### Statistical methods

Baseline characteristics are summarised using descriptive statistics. Unevenly distributed outcome measures are expressed as medians and inter-quartile ranges. A differential effect among the four included vascular diseases is not expected, as the primary outcome is SDM. SDM is equally applicable to each of these diseases since multiple treatment options are available. Nevertheless, the sample size is sufficient to analyse the effect on SDM for each disease separately.

Differences in mean scores of the 5-item OPTION instrument between consultations in which usual care is provided (control group) and the consultations in which DSTs are used (intervention group), are analysed using the Student t-test with Satterthwaite correction for unequal variances. ANCOVA is applied to correct for possible baseline differences in patients before and after the introduction of the DSTs.

Differences in (semi-)continuous variables between the usual care group and the DSTs group (e.g. Likert scales and quality of life scores) are analysed by means of the Student t-test or the non-parametric Mann-Whitney U test, depending on the normality of their distribution. Percentages are compared using a Chi-square test (e.g. for the final treatment choice). In particular, before-after differences in DCS at 4 weeks are analysed after correcting for differences between the groups in baseline DCS. Logistic regression analysis is used to determine the individual effect of the different DSTs on our primary outcome. Statistical analyses will be conducted using IBM SPSS version 24 (IBM, Armonk, NY, USA).

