**Table 1 Tab1:**
[figure not shown]
Multicentre stepped-wedge cluster-randomised design

-: Before introduction of decision support tools

+: After introduction of decision support tools

: Introduction of decision support tools/evaluation moment

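### The primary-analysis sentence groups consultations by actual DST use, while other sections group by introduction or receipt; only the timing of introduction is randomised, so the wording must be reconciled

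*Protocol article*

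**What the plan says.** The protocol article describes the intervention group in three ways.

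- **By use.** Statistical methods states the primary contrast as one "between consultations in which usual care is provided (control group) and the consultations in which DSTs are used (intervention group"). The Interventions section has similar wording: "Use of the DSTs is compared to standard care at the level of individual participants".
- **By introduction.** Table 1 labels its two conditions as before introduction and "After introduction of decision support tools". Sample size is based on "a clinically relevant difference in the use of SDM during consultation before and after introduction of the DSTs". In Statistical methods, the sentence directly after the primary contrast reads "ANCOVA is applied to correct for possible baseline differences in patients before and after the introduction of the DSTs".
- **By receipt.** Participants' timeline says "Patients in the intervention group receive the decision aid prior to the appointment at the outpatient clinic", and the Abstract likewise has the intervention group receiving the tools.

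The Allocations section says what is randomised: after centres are drawn into clusters, further lots are drawn "to decide which cluster is next to start applying the DSTs". Use after that point varies. Centres may choose their own combination of tools (Interventions). Card use is counted from the recordings as an implementation outcome, and a decision aid counts as successfully used only if the patient completes it (Outcomes). The article does not say where a post-introduction consultation without a card or a completed aid belongs.

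**The concern.** Randomisation protects the comparison of consultations before and after a cluster's crossover. It does not protect a comparison of consultations with and without a tool, because surgeon, centre and patient settle use after the crossover. If surgeons who already involve patients use the cards more often, or patients who want involvement complete the aid more often, the used group will score higher on OPTION even when the tools do nothing. The Discussion already recognises that patients who want an active role may be more willing to take part; the same preference could plausibly drive tool use.

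Card use is also read from the recordings on which OPTION is scored, and the Blinding section says the raters cannot be blinded. Under a by-use rule, group membership would therefore be partly settled from the outcome recording itself. With several definitions in the text, the grouping could also be chosen after the data are seen. What is at stake is whether the primary result is a randomised comparison.

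**Working it through.** **The plan's own figure.** With SDs 14 and 8 (Sample size), two-sided alpha 0.05 (sidedness is not stated) and 90% power, a Satterthwaite t-test needs 29 per group, 58 in total, for a 10-point difference (power 90.4%). Then 58 × 1.944 = 112.8, taken as 113; 113 × 4 = 452; 452/0.9 = 502.2, stated as 502. The total reproduces. The base of 58 matches the Abstract's 10 points; the 11 points in Sample size would need 48. That mismatch is a separate matter. The total does not depend on the group definition, so the question here is which contrast is estimated.

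**Inputs for the bias illustration.**
- SD = √((14² + 8²)/2) = √130 = 11.40, pooled from Sample size.
- Uptake u = share of post-introduction consultations with a tool used. Not in the documents; 0.6 assumed, range 0.5 to 0.9.
- r = correlation between the latent tendency to use a tool and the OPTION score. Not in the documents; 0.2 to 0.3 assumed, with 0.1 also shown.
- True effect zero, equal numbers before and after crossover (452/2 = 226 each), clustering ignored.

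**Formulas.** Let φ be the normal density at the point with upper tail u.
- Mean shift in users: r × SD × φ/u
- Mean shift in non-users: −r × SD × φ/(1 − u)
- Non-users dropped: bias = user shift
- Non-users counted as control: bias = user shift − non-user shift × (1 − u)/(2 − u)
- Non-users kept in the intervention group: u × user shift + (1 − u) × non-user shift = 0

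**At u = 0.6** (φ = 0.3863):
- r = 0.2: users +0.2 × 11.40 × 0.3863/0.6 = +1.47; non-users −2.20. Dropped: 1.47. Counted as control: 1.47 + 2.20 × 0.4/1.4 = 2.10.
- r = 0.3: users +2.20; non-users −3.30. Dropped: 2.20. Counted as control: 2.20 + 3.30 × 0.4/1.4 = 3.15 (3.146 before rounding).

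A simulation under the same assumptions gave 1.44 and 2.21 (dropped), and 2.07 and 3.14 (counted as control).

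**Range** (points; dropped / counted as control):

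| Uptake | r = 0.1 | r = 0.2 | r = 0.3 |
|---|---|---|---|
| 90% | 0.2 / 0.4 | 0.4 / 0.8 | 0.7 / 1.2 |
| 70% | 0.6 / 0.9 | 1.1 / 1.7 | 1.7 / 2.6 |
| 60% | 0.7 / 1.0 | 1.5 / 2.1 | 2.2 / 3.1 |
| 50% | 0.9 / 1.2 | 1.8 / 2.4 | 2.7 / 3.6 |

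A negative r reverses every sign.

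**Effect on type I error.** With the larger SD of 14, r = 0.3, 70% uptake and non-users dropped, the bias is 2.1 points. A nominal 5% error becomes about 11% at 113 patients and 30% at 452, again ignoring clustering.

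**Cost of grouping by phase.** If a non-use consultation gains nothing, the expected difference is u × effect. Power at the base 58 (29 per group, normal approximation) is:

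| Uptake | 11-point effect | 10-point effect |
|---|---|---|
| 100% | 96% | 92% |
| 90% | 91% | 85% |
| 80% | 84% | 76% |
| 70% | 73% | 65% |
| 50% | 45% | 39% |

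**The case against.** The strongest reply is that the by-use clause is loose wording for the intervention phase. Table 1, Sample size and the very next sentence of Statistical methods speak of introduction, and the Abstract and timeline speak of receipt, which precedes any use in the consultation. The practical training is itself listed as a DST and is offered to all surgeons just before their centre starts, so a post-introduction consultation fits the description of standard care poorly even when no card is used. Actual use has its own place as an implementation outcome, and a separate regression addresses the individual tools, which suits a primary comparison by phase. The Interventions sentence mainly describes the comparator and the level of comparison.

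Much of this stands. A reader might infer that the plan has settled on an as-treated analysis that discards randomisation and selects for surgeons and patients who favour SDM. The documents do not support that. By-use grouping is one reading of one clause, and dropping non-use consultations or counting them as control is nowhere stated. Selection is an inference, and its sign is not fixed: tools might be used more in difficult or low-engagement consultations.

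The reply does not remove the conflict. The operative sentence for the primary outcome names use, the Interventions section does too, training is offered and not stated to be compulsory, and no passage says which definition prevails. This is a stated rule at odds with the rest of the article, not a detail left to a fuller document.

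**Conclusion.** The point holds as a contradiction in the definition of the primary comparison. If the by-use sentence is followed literally, the comparison is non-randomised and could be biased, probably but not certainly towards the DSTs. In the illustration (60% uptake, r of 0.2 to 0.3, SD 11.4, no true effect), the bias of 1.5 to 3.1 points is 15 to 31% of the 10-point target in the Abstract, or 14 to 28% of the 11 points in Sample size. At 90% uptake and r = 0.1 it is 0.2 to 0.4 points. It is zero if non-use consultations stay in the intervention group. Uptake and correlation are assumptions, so these figures show what the ambiguity could cost and do not estimate what it will cost. The contradiction itself rests on no assumption.

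**What to change.** Reconcile the passages on the randomised phase. Assign every included consultation to its cluster's phase, before or after the crossover date, whether or not a tool was used, and make this the primary comparison. Reword the primary-contrast sentence in Statistical methods and the comparison sentence in Interventions to match Table 1, Sample size and the ANCOVA sentence. Report the by-use comparison only as secondary and label it non-randomised. State also how a decision is classed when its consultations straddle the crossover date, since the plan scores several consultations as one.

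If phase was meant all along, the cost is wording only. If grouping by use was intended, low uptake dilutes the estimate. On the pessimistic assumption that non-use consultations gain nothing, 70% uptake turns 11 points into 7.7 and takes power at the base 58 from 96% to 73%. The diluted estimate is still the one that answers whether introducing the DSTs improves SDM. The expected uptake should be stated and the sample size checked against it.
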